**Figure 1 F1:**
[figure not shown]
Flowchart of trial timeline.

PET imaging will be undertaken at screening ([^18^F]F-DOPA), baseline ([^18^F]FE-PE2i) and then month 6 ([^18^F]F-DOPA), month 12 ([^18^F]F-DOPA and [^18^F]FE-PE2i), month 24 ([^18^F]F-DOPA and [^18^F]FE-PE2i), and month 36 ([^18^F]F-DOPA and [^18^F]FE-PE2i) following surgery.

Major motor and cognitive assessments in both ON and OFF DA medication states will be undertaken at baseline, month 6, month 12, month 24 and month 36 following surgery.

The schedule of assessments is summarised in table 2.

**Table 2 T2:** Schedule of assessments over the course of the trial

Assessment	Screening	Baseline	Day before surgery	Surgery day 0	Days							Months												
Visit	Day −120 to day −7	Day −60 to day −1			1	2	7	14	21	28	42	2	3	4	5	6	9	12	15+*	18	24	30	36	
**General**																								
Informed consent	X																							
Assessment of eligibility	X																							
Concomitant medication (including PD medication)	X	X	X	X	X	X	X	X	X	X	X	X	X	X	X	X	X	X	X	X	X	X	X	
Height	X																							
Weight	X	X	X				X	X	X	X	X	X	X	X	X	X	X	X	X					
ECG		X				X																	X	
Vital signs		X		X	X	X	X	X	X	X	X	X	X	X	X	X	X	X	X	X	X	X	X	
Physical examination	X	X					X	X	X	X	X	X	X	X	X	X	X	X		X	X	X	X	
Demographics	X																							
Medical history	X																							
Years of education	X																							
Smoking status	X																							
AE assessment	X	X		X	X	X	X	X	X	X	X	X	X	X	X	X	X	X	X	X	X	X	X	
Pregnancy test†	X	X	X							X		X	X	X	X	X	X	X		X				
Provision of participant contact/alert card		X																						
Review nIMP compliance							X	X	X	X	X	X	X	X	X	X	X	X	X	X				
Enrolment to long-term F/U																							X	
**Biological samples**																								
FBC	X		X‡		X	X	X	X	X	X	X	X	X	X	X	X	X	X						
U&E	X		X‡		X	X	X	X	X	X	X	X	X	X	X	X	X	X						
Tacrolimus/ciclosporin level§					X	X	X	X	X	X	X	X	X	X	X	X	X	X						
LFTs	X		X‡		X	X	X	X	X	X	X	X	X	X	X	X	X	X						
Coagulation tests	X		X‡																					
CRP	X		X‡		X	X	X	X	X	X	X	X	X	X	X	X	X	X						
Cross-match testing			X‡																					
Microbiology/serology	X																							
HLA antibody titres¶	X												X			X	X	X		X	X	X	X	
Glucose	X		X‡		X	X	X	X	X	X	X	X	X	X	X	X	X	X		X				
HbA1c	X		X‡										X			X	X	X		X				
Blood lipids	X		X‡		X		X	X		X		X	X			X	X	X		X				
TPMT	X																							
MRSA (Cambridge participants only)	X																							
Research blood sample (optional)		X														X				X			X	
Lumbar puncture for CSF collection and accompanying blood sample** (optional)		X														X				X				
**Imaging**																								
MRI (screening)	X																							
MRI (surgical planning)		X																						
CT angiogram		X																						
MRI (with frame)				X																				
MRI (safety)						X				X		X	X			X††	X	X††			X††		X††	
MRI (extended battery)		X														X‡‡		X‡‡			X‡‡		X	
PET scan (F-DOPA)§§	X															X‡‡		X			X‡‡		X	
Done (PE2i)§§		X																X‡‡			X‡‡		X	
MDS-UPDRS part III¶¶	X ON+OFF	X ON+OFF											X ON			X ON+OFF	X ON	X ON+OFF		X ON	X ON+OFF	X ON	X ON+OFF	
MDS-UPDRS parts I, II and intravenous	X	X											X			X	X	X		X	X	X	X	
9 hole peg test¶¶		X ON+OFF											X ON			X ON+OFF	X ON	X ON+OFF		X ON	X ON+OFF	X ON	X ON+OFF	
Timed sit-stand-walk test¶¶		X ON+OFF											X ON			X ON+OFF	X ON	X ON+OFF		X ON	X ON+OFF	X ON	X ON+OFF	
Hauser patient diary card***		X											X			X	X	X		X	X	X	X	
RUSH dyskinesia scale¶¶		X ON+OFF											X ON			X ON+OFF	X ON	X ON+OFF		X ON	X ON+OFF	X ON	X ON+OFF	
AIMS¶¶	X ON+OFF	X ON+OFF											X ON			X ON+OFF	X ON	X ON+OFF		X ON	X ON+OFF	X ON	X ON+OFF	
30 s tap test¶¶		X ON+OFF											X ON			X ON+OFF	X ON	X ON+OFF		X ON	X ON+OFF	X ON	X ON+OFF	
PKG***		X											X			X	X	X		X	X	X	X	
L-dopa challenge test¶¶		X														X		X			X		X	
**Cognitive assessments**																								
MoCA	X ON															X ON		X ON			X ON		X ON	
Pentagon copying	X ON																							
Semantic (animal naming) fluency†††	X ON																							
HVLT-R		X ON																					X ON	
Stroop test		X ON																					X ON	
Digit span test		X ON																					X ON	
WAIS similarities test		X ON																					X ON	
Boston naming task		X ON																					X ON	
**Psychiatric assessments**																								
MADRS	X	X								X			X			X		X			X		X	
Non-motor/QOL assessments																								
PDQ-39		X																	X			X		X
EQ-5D-5L		X																	X			X		X
PD NMSS		X																	X			X		X
TREATMENT																								
Surgery (transplantation of STEM-PD product)				X																				
nIMPs			As prescribed (including tapering)																					

‘ON’ or ‘OFF’ dopaminergic medications are indicated for clinical assessments at each stage.

* The 15+ month visit will occur within 2 weeks of the participant completing their course of immunosuppressants. If the completion of immunosuppressants is within 2 weeks of the scheduled 18-month post-surgery visit, then this visit and the assessments listed will not take place.

† To be performed for female participants of childbearing potential only. At screening, a serum pregnancy test will be performed, and on all subsequent visits, either a serum or urine pregnancy test will be performed at the site’s discretion. Monthly urine pregnancy tests will be performed by participants at home at months 7, 8, 10, 11, 13, 14, 15, 16 and 17. A member of the trial team will contact the participant to confirm the pregnancy test has been performed and record the result.

‡ Samples will not need to be repeated on day −1 if performed within the 3 days prior to this visit, ie, to day −4). Blood typing does not need to be repeated.

§ To be performed depending on which immunosuppressant treatment the participant is on, that is, if the participant is on tacrolimus treatment, then the tacrolimus level will be tested, and if on ciclosporin A, the CyA level will be tested.

¶ At screening, will include a screening test of anti-HLA antibodies. If positive, a specific assessment of any major histocompatibility complex (MHC) class I antigens against those expressed in the STEM-PD product will be carried out. For all other visits, HLA antibodies will be monitored.

** Where possible, blood analysis will be performed on samples already collected.

†† For visits completed in Lund, this will be done simultaneously with the extended battery MRI

‡‡ Optional for Cambridge participants.

§§ Low dose CT scans will be performed in conjunction with each positron emission tomography scan performed at RS-SUS.

¶¶ To be videoed with the participant wearing a cap.

*** Hauser patient diary cards and PKG will be provided to participants ahead of the visit to enable completion of data prior to the visit. At the visits, the trial team will collect in the Hauser patient diary cards and PKG, as outlined in STEM-PD SOP4: Motor and Cognitive Assessments. PKG for Lund participants only.

††† The semantic (animal naming) fluency assessment may also be videoed if required by the site to assist with scoring.

AE, adverse event; CRP, C reactive protein; CSF, cerebrospinal fluid; EQ-5D-5L, Euroqol questionnaire; FBC, full blood count; F-DOPA, [18F]-fluorodopa; F/U, follow-up; HbA1c, glycated haemoglobin; HLA, human leucocyte antigen; HVLT-R, Hopkins Verbal Learning Test - Revised; LFT, liver function tests; MADRS, Montgomery-Åsberg Depression Rating Scale; MoCA, Montreal Cognitive Assessment; MRSA, Methicillin-resistant Staphylococcus aureus; nIMP, non-investigational medicinal product; NMSS, Non-Motor Symptoms Scale; PD, Parkinson’s disease; PDQ-39, Parkinson's disease Questionnaire 39; PKG, Parkinson’s KinetiGraph; QOL, quality of life; TPMT, hiopurine methyltransferase; U&E, urea and electrolytes; WAIS, Wechsler Adult Intelligence Scale.

### Assessments to be undertaken

Occurrence of adverse events (AEs) and SAEs will be recorded as is standard in all clinical trials. AEs of special interest will also be collected and include:

Stroke.Major intracranial haemorrhage.Central nervous system infection.Major worsening of the participant’s PD or rapid and substantial worsening of their existing dyskinesias that does not respond to a reduction in dopaminergic therapy.Clinically significant event which may be related to immunosuppressive treatment, such as atypical infections, malignancies (squamous skin cancer, Kaposi’s sarcoma and lymphomas) and metabolic events (osteoporosis, diabetes).Any event occurring up to 24 hours post-transplantation (not including well-known surgery-related events, eg, nausea, malaise).

Clinical assessments will be undertaken to evaluate changes between baseline and month 36 post-transplantation in four domains: global cognitive measures, non-motor/quality of life assessments, motor features in the OFF DA medication state and PD medications. The assessments to be undertaken are summarised in table 3. The motor assessments will be video recorded, such that they can be rated by a blinded independent rater, as was done in the TransEuro fetal DA cell transplant trial.^17^

**Table 3 T3:** Clinical assessments to be undertaken in four domains at baseline and month 36 following transplantation

Global cognitive changes	Non-motor/quality of life assessments	Motor features in the OFF dopamine medication state	Parkinson’s disease medications
Montreal Cognitive Assessment	PDQ-39: overall total+subscale totals	MDS-UPDRS part III: total score	L-dopa equivalent dose
Hopkins Verbal Learning Test-Revised	EQ-5D-5L VAS score	AIMS: total score+dichotomous >2 points in one body part	L-dopa yes/no
Stroop	EQ-5D-5L: individual scores for each dimension	9 hole peg test: separately for each side, mean of two rounds	
Digit span	NMSS: overall total+total score per domain	Timed sit-stand-walk: one value (seconds)	
Wechsler Adult Intelligence Scale similarities	MADRS score: total score at baseline and 36 months	Hauser diary card: percentage of waking time. Mean of 3 days for four parameters (ON with troublesome dyskinesia, ON with non-troublesome dyskinesia, ON without dyskinesia, OFF)	
Boston naming task	MADRS dichotomous >20 at 36 months	RUSH dyskinesia: Off dyskinesias and total dyskinesia score	
		30 s tap test: separately for each side, mean of two rounds	
		Parkinson’s KinetiGraph (PKG)—wrist-worn accelerometer readings (Lund participants only)	

AIMS, Abnormal Involuntary Movement Scale; EQ-5D-5L, EQ-5D-5L - Euroqol questionnaire; MADRS, Montgomery-Åsberg Depression Rating Scale; NMSS, Non-Motor Symptoms Scale; PDQ-39, Parkinson's disease Questionnaire 39; VAS, Visual Analogue Scale.

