## Methods and analysis

### Overview

The STEM-PD trial is a multi-centre, single-arm, dose-escalation, first-in-human advanced therapy investigational medicinal product (ATIMP) trial. The aim of the study is to assess the safety, tolerability and feasibility of intraputamenal transplantation of the STEM-PD product in patients with moderately advanced PD.

Participants will be patients with moderately advanced PD who have been followed up for at least 12 months as part of the TransEuro observational study and who meet all inclusion and exclusion criteria as outlined in table 1^13^.

**Table 1 T1:** Inclusion and exclusion criteria for the trial

Inclusion criteria	Exclusion criteria
Have given written informed consent to participate in the trial	Tremor dominant disease, as assessed by the PI or other delegated clinician
Diagnosed with PD as defined using Queen Square Brain Bank criteria	Significant drug-induced dyskinesias as defined by a score of ≥2 in the Abnormal Involuntary Movement Scale (AIMS) dyskinesias rating scale, in any body part in the ON state
Moderate disease as defined by having Hoehn and Yahr stage 2–3 in OFF state	Ongoing major medical or psychiatric disorders, including depression (MADRS>20) and psychosis, or other medical unsuitability, as judged by the PI or other delegated clinician
Disease duration >10 years	Any contraindication to neurosurgery
Male or female, aged between 50 and 75 years (inclusive)	Unable to be imaged using MRI
Have a significant response to dopamine therapies as judged by the PI or other delegated clinician	Extensive ventral striatal loss or normal findings on F-DOPA PET at screening
Have symptoms that are not appropriately controlled by existing oral anti-PD medications, as judged by the PI or other delegated clinician	Significant cognitive impairment indicative of an incipient dementia/established dementia or values consistent with MoCA score of ≤24
Ability to travel to Lund for surgery	Unable to perform normal copying of interlocking pentagons and/or a semantic fluency score for naming animals of less than 20 over 90 s
Followed up for at least 12 months prior to inclusion in this trial in the TransEuro observational study	
Be fluent in English/Swedish to enable completion of questionnaires as assessed by the PI or other delegated clinician at Cambridge/Lund, respectively	
Be approved by the TMG clinical subgroup for trial participation	

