### Secondary outcomes

The secondary objectives of the trial will be:

To evaluate the course and efficacy of the clinical features following intraputamenal transplantation of the STEM-PD product in patients with moderate PD.To assess the survival of DA cells following transplantation of the STEM-PD product in patients with moderate PD using PET imaging.To determine the safety and clinical efficacy between doses (if dose escalation is undertaken) of the STEM-PD product, including an assessment as to whether there is a dose–response effect.

The following secondary outcome measures will therefore be collected:

Changes in clinical measures at 36 months following transplantation compared with baseline (including emergence of new neurological features, including GIDs, global cognitive changes and changes in non-motor/quality of life assessments).Changes in motor features in the OFF state at 36 months.Change in anti-Parkinson medication as measured by L-dopa equivalent dose at 36 months.[^18^F]F-DOPA uptake and DA transporter (DAT) binding (using [^18^F]FE-PE2i imaging) at 36 months on PET imaging with [^18^F]F-DOPA and [^18^F]FE-PE2i compared with PET imaging performed pre-transplant.The number and nature of SAEs and AEs in the 12–36 months period following transplantation.

The secondary outcome measures will be reported with descriptive statistics for measurements at baseline and at 36 months. Absolute and relative differences will also be presented. MDS- UPDRS part III in ON and OFF state, AIMS sum score and PDQ-39 will also be described using line charts for all available time points.

[^18^F]F-DOPA PET imaging will be reported as absolute measurements of DA storage capacity measured by [^18^F]F-DOPA influx rate (K_i_), and relative measurements as measured by standardised uptake value ratios (SUVR) with occipital and/or cerebellar reference regions. K_i_ and SUVR values will be reported per brain hemisphere and per region of interest (ROI) in basal ganglia subregions, including the nucleus accumbens, pre-commissural ventral putamen, post-commissural ventral putamen, pre-commissural dorsal putamen and post-commissural dorsal putamen.

[^18^F]FE-PE2i-PET imaging will be reported as absolute measurements of DAT binding as ascertained using *BP*_ND_, and relative measurements as calculated using SUVR with occipital and/or cerebellar reference regions. The *BP*_ND_ and SUVR values will be assessed in the same ROIs as described for [^18^F]F-DOPA .

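### Graft-induced dyskinesia would be recorded, but the yes/no measure tied to month 36 and an adverse-event category limited to existing dyskinesias could under-classify it or fail to flag it

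*Protocol article*

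**What the plan says.** All references are to the protocol article.

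- **Yes/no measure.** Table 3 lists "AIMS: total score+dichotomous >2 points in one body part" under the column "Motor features in the OFF dopamine medication state". The table is titled "Clinical assessments to be undertaken in four domains at baseline and month 36 following transplantation".
- **GID as an outcome.** Secondary outcomes lists "Changes in clinical measures at 36 months following transplantation compared with baseline (including emergence of new neurological features" and then names GIDs among those features. Descriptive statistics for secondary outcomes are planned for baseline and 36 months. The AIMS sum score is additionally charted at all available time points.
- **AESI.** Under Assessments to be undertaken, the dyskinesia item is "rapid and substantial worsening of their existing dyskinesias that does not respond to a reduction in dopaminergic therapy", offered as an alternative to major worsening of the participant's Parkinson's disease.
- **Entry rule.** Table 1 excludes "Significant drug-induced dyskinesias as defined by a score of ≥2 in the Abnormal Involuntary Movement Scale (AIMS" when that score is found "in any body part in the ON state".
- **Visits.** Table 2 schedules AIMS and RUSH after surgery at months 3, 6, 9, 12, 18, 24, 30 and 36, with OFF ratings at months 6, 12, 24 and 36.
- **Background.** The Introduction describes GIDs as new involuntary movements, in a few patients severe enough to need further neurosurgery. Statistical considerations supports the trial's size partly by saying that trials this small have identified GIDs.

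**The concern.** GID is the graft-specific harm that the article itself singles out, and comparing safety between the two doses is a secondary objective. The rules that turn dyskinesia data into counts therefore matter, and three of them lean towards fewer counted or flagged cases.

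First, emergence can happen at any visit, but the yes/no measure is read at one post-graft visit. Second, the AESI wording covers dyskinesias that a participant already has, in a population selected for having little ON-state dyskinesia, while the harm of interest is new. Third, the outcome cut-off sits one step above the value that the entry criteria call significant, and its unit is unclear. At stake is whether the yes/no dyskinesia count and the AESI listing understate a harm that the rest of the data would show.

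**Working it through.** The article states no GID rate, power or alpha, so there is no planned figure to reproduce. The check compares its rules with each other.

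**1. Timing.** From the AIMS row of Table 2:

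| | Post-graft visits | Used by the yes/no measure | Not used |
|---|---|---|---|
| All AIMS visits | 8 (months 3, 6, 9, 12, 18, 24, 30, 36) | 1 (month 36) | 8 − 1 = 7 |
| With an OFF rating | 4 (months 6, 12, 24, 36) | 1 (month 36) | 4 − 1 = 3 |

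A participant negative at baseline, positive OFF at month 12 and negative again at month 36 is a non-event.

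**2. AESI.** Side by side, the Introduction describes GIDs as new movements, Table 1 excludes significant ON-state drug-induced dyskinesia, and the AESI requires dyskinesias that already exist. A participant with none before grafting who develops a GID does not meet the dyskinesia wording.

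**3. Cut-off.** The article does not give the AIMS item range; whole-number items from 0 to 4 are assumed.

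| Body-part score | Entry rule (≥2, ON) | Outcome (>2, OFF), read as a score |
|---|---|---|
| 0, 1 | no | no |
| 2 | yes | no |
| 3, 4 | yes | yes |

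Only a score of exactly 2 is treated differently. If the outcome instead means a change of more than 2 points, then from a baseline of 0 or 1 the moves 0→2, 1→2 and 1→3 all reach 2 or more without being counted (changes of 2, 1 and 2). Only 0→3, 0→4 and 1→4 are counted.

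Elsewhere the article keeps one cut-off for both purposes: MADRS above 20 is the exclusion value in Table 1 and the dichotomy in Table 3.

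**4. Size.** One participant reclassified from case to non-case changes a cohort from 1/4 = 25% to 0/4, or the pooled figure from 1/8 = 12.5% to 0/8.

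As an illustration, let p be the true GID risk and f the share of GIDs that the yes/no measure counts. Both are assumptions. With n = 8, P(at least one counted) = 1 − (1 − pf)^8.

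| | f = 1 | f = 0.75 | f = 0.5 | f = 0.25 |
|---|---|---|---|---|
| p = 0.20 | 0.83 | 0.73 | 0.57 | 0.34 |
| p = 0.10 | 0.57 | 0.46 | 0.34 | 0.18 |

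For example, 1 − 0.8^8 = 0.83 and 1 − 0.9^8 = 0.57.

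**The case against.** A reader might infer that the trial would miss GIDs. The article does not support that. All adverse events are primary outcomes to month 12 and secondary outcomes from month 12 to 36. The AIMS sum score is charted at every available visit, RUSH scores carry no cut-off, motor assessments are videoed for a blinded rater, and clinical evaluations are reviewed at 6 months before escalation. This stands: GIDs would be recorded. What it does not supply is a count of new cases. A sum score does not show whether one body part crossed a threshold, the article does not state the medication state of the charted AIMS score, and RUSH is not among the charted measures. Statistical considerations does say that tables are presented separately for each time point, but for secondary outcomes the stated time points are baseline and 36 months.

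A reader might also infer that ≥2 and >2 contradict each other. They do not strictly: one is an ON-state eligibility rule for drug-induced dyskinesia, the other an OFF-state outcome. Entry sets no OFF-state limit, so OFF scores at baseline need not be 0 or 1. What remains is an unexplained difference and an ambiguous unit.

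Nor does the article call the AIMS dichotomy a GID rate or a headline result. It is part of one cell among secondary measures, in a descriptive trial with no decision attached to it. The AESI list is introduced as open, its other limb might catch some cases, and the temporary-halt rule does not depend on AESI status. All of this stands and limits the weight of the point. It does not change the fact that new-onset dyskinesia is unnamed. A full GID case definition may sit in the full protocol or analysis plan; its absence from an article is not the complaint here.

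**Conclusion.** The concern holds as a matter of classification and flagging, not of detection. Under the stated rules, a transient or treated GID drops out of the only yes/no dyskinesia measure, and a new-onset GID falls outside the dyskinesia wording of the AESI. The cut-off needs an explanation and a unit, but the article does not show that either value is wrong.

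The effect is one participant at a time: 25 percentage points in a cohort of four and 12.5 in the pooled eight. The probabilities above rest on assumed risks and counted shares and only show direction. The direction is one-sided, since each rule can leave a case uncounted or unflagged. That, with the low cost of correction, makes this worth changing, though nothing in the primary outcome depends on it.

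**What to change.** 1. Report the dichotomous AIMS outcome as first occurrence at any post-graft OFF-state visit to month 36 in participants in whom it was absent at baseline, with the visit of onset, alongside the month-36 value.
2. Word the AESI to include new-onset as well as worsening dyskinesias.
3. State whether the AIMS outcome is a score or a change from baseline, and reconcile or justify it against the ≥2 entry cut-off. That choice is the investigators'. Tabulating each participant's maximum body-part score by visit and medication state would let both cut-offs be read.

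**Cost.** These are wording changes on assessments already scheduled. The count of new cases can only stay the same or rise, and a few more AESI reports may arise.

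**Timing.** Grafting ran from February 2023 to October 2024, so month-36 readings fall between February 2026 and October 2027, after the article's publication in December 2025. Month-12 visits fell due by October 2025, so the change should be dated and described as made after those visits. Earlier events in the adverse-event log can be re-tabulated under the revised AESI wording.
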